#### 2.5.5. Biomarkers

Venous blood and urine samples for biomarker analysis were collected at 3 timepoints: baseline (i.e., after consent and prior to randomization) and at three and six months following randomization. Blood samples were collected in serum separation BD Vacutainer^®^ SST™ (Becton, Dickinson and Company, Franklin Lakes, NJ, USA) Tubes, immediately chilled, and then centrifuged as soon as possible at 2500× *g* and 4 °C for 10 min. The samples were aliquoted and stored at −80 °C at the laboratory of Experimental Cardiology (IDIBAPS, Barcelona, Spain) until batch analysis. Upon completion of the trial, the samples were analyzed to determine the concentration of C-terminal propeptide of type I procollagen, N-terminal propeptide of type III procollagen, Galectin-3, and Suppression of Tumorigenicity 2. The levels of C-terminal propeptide of type I procollagen and N-terminal propeptide of type III procollagen were determined by an enzyme-linked immunoassay (ELISA) kit (Elabscience Biotechnology Co., Ltd., Houston, TX, USA). Galectin-3 and Suppression of Tumorigenicity 2 were determined by a bead-based multiplex immunoassay (R&D Systems, Inc., Minneapolis, MN, USA).

#### 2.5.6. Drug Discontinuation During the Trial

Participants who initiated an open-label SGLT2i or who were withdrawn from the trial were asked to complete the follow-up CMR.

### 2.6. Trial Outcomes

The primary, secondary, and exploratory outcomes will be measured as the change from baseline to 6 months of follow-up (Figure 1). Differences between the dapagliflozin and placebo groups in these changes will be analyzed. All CMR measurements will be indexed to body surface area, calculated at the time of the scan using the Mosteller formula.

*Primary outcome*

The primary endpoint is the change in ECV of the remote myocardium from baseline to six months, as measured by CMR.

*Secondary outcomes*

These include changes in the circulating biomarkers from baseline to six months: C-terminal propeptide of type I procollagen;N-terminal propeptide of type III procollagen;Galectin-3;High-sensitivity troponin I.

*Exploratory outcomes*

The exploratory outcomes include changes in other CMR measures of cardiac function and remodeling from baseline to six months, including: Left ventricular end-diastolic and end-systolic volumes;Left ventricular mass;Left ventricular ejection fraction.

They also include changes in other circulating biomarkers from baseline to six months and clinical events:N-terminal pro-B-type natriuretic peptide.Suppression of Tumorigenicity 2.Rate of major adverse cardiovascular events (MACE), including cardiovascular death, non-fatal myocardial infarction, non-fatal stroke, and heart failure hospitalization. All these endpoints will be adjudicated independently by a clinical event committee (CEC) (Supplementary Materials).Adverse events (AEs) and serious AEs were actively collected at follow-up visits and through spontaneous reporting by participants during the study. AEs of interest were represented by severe hypoglycemia, acute kidney injury, acute liver function profile impairment, severe dehydration, symptomatic and sustained hypotension, complicated genitourinary infections, diabetic ketoacidosis, and diabetic foot complications (in diabetic patients). AEs were recorded using a standardized form and assessed for severity, causality, and expectedness. All adverse events were communicated to the DSMB.Change in body weight from baseline to six months.

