### 2.4. Screening

Transthoracic echocardiograms were performed during routine clinical care for participants presenting with their first clinically diagnosed STEMI undergoing primary PCI to identify those with an LVEF ≤ 50%, measured by Simpson’s Biplane or estimated by visual assessment. Participants meeting the inclusion criteria and none of the exclusion criteria were approached by study investigators at each site to obtain consent. Consenting participants underwent a baseline CMR scan. Participants with an LVEF ≤ 50% on CMR were randomized, while those with an LVEF > 50% were excluded. To minimize the influence of baseline myocardial fibrosis developed before randomization, being maximal between 2 and 8 weeks after the index event [8], the baseline CMR was required to be performed within 15 days following STEMI, preferably before hospital discharge.

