### 2.5. Trial Procedures

#### 2.5.1. Randomization and Blinding

Participants were randomized in a 1:1 ratio to receive dapagliflozin 10 mg daily (intervention) or a placebo (control). The randomization schedule was generated by an independent statistician using a computer-based program for stratified randomization, incorporating two stratification variables (i.e., presence of T2DM and infarction site) to ensure a balanced distribution across treatment groups. Participants were enrolled by the study investigators at each site after eligibility was confirmed and informed consent obtained. The trial pharmacist, who had exclusive access to the allocation codes, assigned participants to the intervention or control group. Randomization was stratified by the presence of T2DM (defined as an established diagnosis, glycated hemoglobin [HbA1c] ≥ 6.5% at index admission, fasting blood sugar ≥ 126 mg/dL, or 2 h blood sugar ≥ 200 mg/dL) and localization of the MI (anterior vs. non-anterior) [9]. Before randomization, baseline assessments were conducted, including weight and height measurement, a physical examination, a 12-lead electrocardiogram, standard laboratory tests (kidney function, liver function, HbA1c, full blood count), and biomarker sample collection. Randomization and administration of the first trial drug dose occurred within 24 h of the baseline CMR study.

The trial employed a quadruple-blind design to ensure that participants, care providers, outcome assessors, and data analysts were unaware of the treatment allocation. Emergency unblinding was permitted only in situations where knowledge of the participant’s allocation group was essential for managing a serious adverse event or a critical medical situation. The unblinding procedure required the treating physician to contact the trial pharmacist responsible for managing the randomization codes. The randomization code was disclosed solely for the specific participant, and the reason for unblinding was thoroughly documented and reported to the DSMB. Measures were taken to ensure that the study team remained blinded to the allocation, except the treating physician directly involved in the emergency management.

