## 3. Statistical Considerations

Based on previous studies conducted by this research group [2,4], it was determined that the change in the ECV of the remote myocardium, measured by cardiac magnetic resonance, between baseline and six months of follow-up in patients with STEMI was 1.5%, with a standard deviation of 2.2%. Assuming a change of 1.5% ± 2.2 in the ECV for the placebo group and an 85% relative reduction in the experimental group, the inclusion of 94 participants (47 per group) would have provided an 80% power to detect such a difference, with an alpha error of 0.05. To account for a 20% loss to follow-up and to ensure balanced groups for stratification based on two variables with two categories each, the final sample size was set at 120 participants (60 per treatment group). After premature termination of the study, a statistical power recalculation was conducted with the same assumption, finding that the final sample of 54 patients would provide 55% power to detect such a difference, with an alpha error of 0.05.

Analyses will be conducted on an intention-to-treat basis. The primary analysis will compare the mean change in ECV of the remote myocardium from baseline to six months between treatment groups (ΔECV dapagliflozin vs. ΔECV placebo) using Student’s t-test or a Mann–Whitney U test, depending on whether the variable has a normal distribution. In addition, a sensitivity analysis will be performed with a mixed model for repeated measures. Similar methods will be used for the analysis of secondary and exploratory outcomes, including changes in circulating biomarkers and other CMR-derived parameters. The mean differences will be reported along with 95% confidence intervals and two-sided *p*-values. Missing data will be handled by the last-observation-carried-forward methodology, while baseline missing data will be considered to be permanently missing. A detailed statistical analysis plan will be finalized prior to database locking and unblinding of the randomized groups.

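### Troponin I is tested as change from a sample taken within about 15 days of the infarct, with no stated transformation or baseline adjustment, so the test probably has very little power

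*Protocol article*

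**What the plan says.** **Endpoint.** Section 2.6 of the protocol article lists four secondary biomarkers, ending with "Galectin-3;High-sensitivity troponin I". NT-proBNP is exploratory. The metric is the same for all: "The primary, secondary, and exploratory outcomes will be measured as the change from baseline to 6 months of follow-up".

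**Baseline timing.** Section 2.5.5 puts the samples at "baseline (i.e., after consent and prior to randomization) and at three and six months following randomization". Section 2.4 says "the baseline CMR was required to be performed within 15 days following STEMI, preferably before hospital discharge", and section 2.5.1 says "Randomization and administration of the first trial drug dose occurred within 24 h of the baseline CMR study". The baseline sample therefore falls in the first two weeks or so after the infarct, on a day that differs between patients.

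**Analysis.** Section 3 compares mean change between arms by t-test or Mann–Whitney test, according to normality, with a mixed model for repeated measures as a sensitivity analysis. It then says: "Similar methods will be used for the analysis of secondary and exploratory outcomes, including changes in circulating biomarkers and other CMR-derived parameters". Results are mean differences with 95% confidence intervals. Missing values are filled by last observation carried forward (LOCF). No transformation or baseline covariate is stated.

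**Assays.** Section 2.5.5 begins its list with "Upon completion of the trial, the samples were analyzed to determine the concentration of C-terminal propeptide of type I procollagen" and goes on to the type III propeptide, Galectin-3 and ST2. Troponin I and NT-proBNP are not on it, nor among the standard baseline laboratory tests in section 2.5.1. Section 4.3 counts central analysis of the biomarkers among the trial's strengths.

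**The concern.** Troponin marks myocardial necrosis. A sample taken days after a STEMI reflects infarct size and sampling day, and both vary widely between patients. A drug effect on troponin can appear only in the 3- and 6-month values. If those are much smaller than baseline, subtracting baseline from them buries the signal under variation that arose before treatment began. A null result on this secondary endpoint would then say little about dapagliflozin, although the data to do better are already being collected.

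A second, smaller matter is that the reader cannot tell from the article whether troponin I is measured centrally with the other markers or locally at each site.

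**Working it through.** **1. The plan's own figures.** The article gives no power figure for troponin; its figures concern ECV. The difference is 0.85 × 1.5 = 1.275 with SD 2.2, so n per arm = 2 × (1.96 + 0.84)² × 2.2² / 1.275² ≈ 47, as stated. With 54 patients (27 per arm) the power is 56.7% by the normal approximation and 55.2% by the t distribution, against 55% stated. These figures reproduce. I use 27 per arm below, which assumes that nobody is lost.

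**2. Assumptions for troponin (none is in the article).** Log-normal values. 6-month median 8 units, log-SD 0.6 (varied to 1.0). Baseline median 20 to 3000 units, log-SD 1.0 to 2.0. Log-scale correlation 0.2 to 0.4. True effect at 6 months exp(−0.45) = 0.64, a 36% reduction.

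**3. Raw change.**
- 6-month mean on placebo: 8 × exp(0.6²/2) = 9.58. The effect is 9.58 × (1 − 0.638) = 3.47 units.
- With baseline median m and log-SD 1.0, the baseline SD is m × exp(0.5) × √(e − 1) = 2.161m.
- From baseline alone, the standard error of the arm difference is 2.161m × √(2/27) = 0.588m.
- m = 3000: 3.47 / 1765 = 0.002. m = 40: 3.47 / 23.5 = 0.15. m = 20: 3.47 / 11.8 = 0.30.
- 80% power needs a ratio of about 2.8.

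**4. Log change.** SD = √(SD_B² + SD_F² − 2ρ·SD_B·SD_F), where B is baseline and F is 6 months.
- SD_B = 1.0, ρ = 0.4: √(1 + 0.36 − 0.48) = 0.938. Then z = 0.45 / (0.938 × √(2/27)) = 1.76, power about 41%.
- SD_B = 2.0, ρ = 0.2: √(4 + 0.36 − 0.48) = 1.970. Then z = 0.84, power about 13%.

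**5. ANCOVA of the log 6-month value on log baseline.** Residual SD = SD_F × √(1 − ρ²).
- SD_F = 0.6: 0.588 (ρ = 0.2) or 0.550 (ρ = 0.4). Then z = 2.81 or 3.01, power about 79–84%.
- SD_F = 1.0, ρ = 0.2: 0.980. Then z = 1.69, power about 39%. Log change with SD_B = 1.0 then has SD √(1 + 1 − 0.4) = 1.265, z = 1.31 and power about 26%.

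**6. Simulated power, 27 per arm, 36% reduction, 6-month log-SD 0.6.**

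| Baseline median | t-test, raw change | Mann–Whitney, raw change | t-test, log change | Log ANCOVA |
|---|---|---|---|---|
| 3000 | 2–4% | 4–5% | 13–41% | 78–83% |
| 40 | 5% | 7% | 36% | 80% |
| 20 | 6% | 11% | 36% | 80% |

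ANCOVA falls to about 55% at a 6-month log-SD of 0.8 and to about 37–39% at 1.0.

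**7. A separate simulation with a halved 6-month level** (6-month log-SD 0.8, correlation 0.4, 27 per arm).
- Baseline medians 100 to 10,000, baseline log-SD 1.5: the rank correlation between change and minus baseline is 0.99–1.00. Power is 2–3% (raw t-test), 4–5% (raw Mann–Whitney), 44–45% (log change) and 92–93% (log ANCOVA).
- Baseline median 20, log-SD 1.0: 9%, 17%, 70% and 92%.
- Sixty per arm, as planned, leaves raw change at about 4–5% for the high baselines.

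**8. No true effect.** Rejection on raw change was 2.2–4.6% (t-test) and 4.2–5.2% (Mann–Whitney), so the false-positive rate stays at about 5% or below.

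**The case against.** **The SAP may settle it.** A log scale and covariates are commonly left to the SAP, and section 3 says one will be finalized before database lock. That the change is taken on the raw scale is my inference from the silence on transformation and the reporting of mean differences. This stands, and it is why log-change power is shown too. But the article itself fixes the change metric and the unadjusted tests, and an SAP that follows them inherits the weakness on either scale.

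**A mixed model is planned.** True, and it extends to the biomarkers, which have a 3-month sample. It is only a sensitivity analysis, however, and its scale and covariates are not given.

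**Every troponin value is assumed.** This stands. A sample near day 15 may hold much less of the infarct release, but raw change stays weak even at a baseline only 2.5 times the 6-month level. Nor does ANCOVA guarantee good power: for a true 15% reduction it gives only about 12–18%.

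**Stronger readings the article does not support.**
- *The endpoint cannot show an effect.* Under randomization the contrast in change is still unbiased for the 6-month difference; the problem is power.
- *A chance imbalance in infarct size would pass for a drug effect.* That is ordinary type I error, which step 8 shows is not inflated. Infarct location is also a stratification factor.
- *LOCF puts the acute value at month 6 as a matter of course.* It does so only if the 3-month sample is missing too; otherwise the 3-month value is carried.
- *The abstract contradicts section 2.6 because it omits troponin.* The abstract's list is worded as non-exhaustive.
- *Troponin I was not measured.* A condensed article may leave out an assay, so the gap in section 2.5.5 calls for clarification and proves no more than that.

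**Conclusion.** The point holds as a loss of sensitivity on one secondary endpoint. The stated test of change has about 2–11% power on the raw scale and 13–41% on the log scale, for an assumed 36% reduction with 27 per arm. Log-scale ANCOVA on baseline reaches about 37–83%. The low end of that range belongs to a wide 6-month spread, where the gain over log change is modest. The conclusion rests on baseline troponin being well above the 6-month level and on the assumed spreads and correlations. The same reasoning carries to NT-proBNP if its baseline is similarly raised, but no calculation was made for it. The primary endpoint and its sample size are untouched. The missing assay information is a separate, minor matter of clarity.

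**What to change.** Before the SAP is finalized and the groups are unblinded:

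1. Make the main analysis of troponin I, and likewise of NT-proBNP, an ANCOVA of the log 6-month value on log baseline, time from STEMI to the baseline sample, diabetes status and infarct location. Report a ratio of geometric means with its 95% confidence interval.
2. Give the planned mixed model the same scale and covariates, with the 3- and 6-month values as outcomes.
3. For these two markers, do not carry the baseline value forward when both later samples are missing.
4. Reconcile section 2.5.5 with sections 2.6 and 4.3: state where, when and by which assay troponin I and NT-proBNP are measured, and whether that is done centrally.

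Items 1 to 3 cost only SAP wording and use data the trial already plans to hold, provided the sampling date is recorded. Section 4.4 says no analysis has yet been done, so the change can still be made blind. Item 4 costs a sentence if the assays exist, or two further assays on stored samples if they do not.

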## 3. Statistical Considerations

Based on previous studies conducted by this research group [2,4], it was determined that the change in the ECV of the remote myocardium, measured by cardiac magnetic resonance, between baseline and six months of follow-up in patients with STEMI was 1.5%, with a standard deviation of 2.2%. Assuming a change of 1.5% ± 2.2 in the ECV for the placebo group and an 85% relative reduction in the experimental group, the inclusion of 94 participants (47 per group) would have provided an 80% power to detect such a difference, with an alpha error of 0.05. To account for a 20% loss to follow-up and to ensure balanced groups for stratification based on two variables with two categories each, the final sample size was set at 120 participants (60 per treatment group). After premature termination of the study, a statistical power recalculation was conducted with the same assumption, finding that the final sample of 54 patients would provide 55% power to detect such a difference, with an alpha error of 0.05.

Analyses will be conducted on an intention-to-treat basis. The primary analysis will compare the mean change in ECV of the remote myocardium from baseline to six months between treatment groups (ΔECV dapagliflozin vs. ΔECV placebo) using Student’s t-test or a Mann–Whitney U test, depending on whether the variable has a normal distribution. In addition, a sensitivity analysis will be performed with a mixed model for repeated measures. Similar methods will be used for the analysis of secondary and exploratory outcomes, including changes in circulating biomarkers and other CMR-derived parameters. The mean differences will be reported along with 95% confidence intervals and two-sided *p*-values. Missing data will be handled by the last-observation-carried-forward methodology, while baseline missing data will be considered to be permanently missing. A detailed statistical analysis plan will be finalized prior to database locking and unblinding of the randomized groups.

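### The primary test of change in remote ECV adjusts for neither baseline ECV nor the two stratification factors, so a trial stopped at 54 of 120 patients probably gives up some precision it could keep

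*Protocol article*

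**What the plan says.** Section 3 (Statistical Considerations) sets out the primary comparison: "The primary analysis will compare the mean change in ECV of the remote myocardium from baseline to six months between treatment groups". The test is "Student’s t-test or a Mann–Whitney U test, depending on whether the variable has a normal distribution". Similar methods are to serve the secondary and exploratory outcomes. A mixed model for repeated measures is named as a sensitivity analysis, with no covariates listed.

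Section 2.5.1 describes randomisation as "incorporating two stratification variables (i.e., presence of T2DM and infarction site) to ensure a balanced distribution across treatment groups". The same section and the Figure 1 legend define the second factor as anterior versus non-anterior infarction. Section 3 also gives balance across these strata as one reason for raising the sample size to 120.

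Nothing in the document carries the strata, or baseline ECV as a covariate, into the primary analysis. Section 3 promises a detailed analysis plan before lock and unblinding, and section 4.4 says that no analysis has yet been done.

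**The concern.** A change score fixes the coefficient of baseline at 1. If the regression slope of six-month ECV on baseline ECV is below 1, that over-corrects. A chance difference in baseline ECV between arms of about 27 patients then feeds into the contrast through regression to the mean, and the variance is larger than it need be. ANCOVA estimates the slope from the data.

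The strata raise a second issue. Stratified randomisation balances the arms on T2DM and infarct site. An analysis that omits them leaves their contribution in the error term, so if they predict change in ECV, the standard error is too large.

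Precision is at stake, in a trial that cannot recover its lost recruitment. The choice of test is stated in the protocol itself and is not a detail deferred to the analysis plan.

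**Working it through.** **Inputs from section 3.** "Assuming a change of 1.5% ± 2.2 in the ECV for the placebo group and an 85% relative reduction in the experimental group". The difference is 0.85 × 1.5 = 1.275 percentage points, with SD of change 2.2. Planned: "the inclusion of 94 participants (47 per group) would have provided an 80% power to detect such a difference, with an alpha error of 0.05". Final sample 54 (27 per arm if allocation is equal), stated power 55%, expected loss 20%.

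**Reproducing the plan's figures.**
- n per arm = 2 × (1.960 + 0.842)² × (2.2 / 1.275)² ≈ 46.7, rounded up to 47. This agrees.
- Power at 27 per arm, two-sided 0.05, noncentral t with 52 df: 55.2%. This agrees with 55%.
- With 20% loss (about 43 evaluable), the same unadjusted test has 45.8% power.

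The plan's figures are therefore right, and they describe the unadjusted change-score test.

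**Adjusting for baseline, equal SDs at both visits.** The ANCOVA residual variance is the variance of change × (1 + rho)/2. The document does not give rho, so the values below are assumptions. Powers use a noncentral t with 49 df at 54 patients and 38 df at 43 (treatment, baseline and two stratum main effects).

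| Assumed rho | Variance ratio | Power, 54 complete | Power, 43 evaluable |
|---|---|---|---|
| 0.3 | 0.65 | 73.5% | 63.2% |
| 0.5 | 0.75 | 67.4% | 57.1% |
| 0.7 | 0.85 | 62.0% | 51.9% |
| 0.8 | 0.90 | 59.5% | 49.7% |
| 0.9 | 0.95 | 57.2% | 47.6% |
| Unadjusted | 1.00 | 55.2% | 45.8% |

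A cautious allowance for chance imbalance in three estimated covariates takes off a further 2 to 3 points, which removes the gain near rho 0.9.

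**Unequal SDs.** Let s1 and s2 be the baseline and six-month SDs. Holding the SD of change at 2.2, rho = (s1² + s2² − 4.84) / (2·s1·s2), and the ANCOVA residual variance is s2²(1 − rho²). The SDs are again assumptions:
- 2.5 and 3.0: rho = 10.41/15 = 0.694; residual 9 × 0.518 = 4.67; ratio 4.67/4.84 = 0.96.
- 2.0 and 3.0: rho = 8.16/12 = 0.68; residual 9 × 0.538 = 4.84; ratio 1.00, so no gain.
- 3.0 and 2.5: rho = 0.694; residual 6.25 × 0.518 = 3.24; ratio 0.67.

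The gain vanishes when the slope rho × s2/s1 is about 1, as in the second case (0.68 × 1.5 = 1.02). Simulations of 20,000 trials at 27 per arm, adjusting for baseline and one non-prognostic covariate, gave 54.9% adjusted against 54.9% unadjusted in the first case, and 54.1% against 55.6% in the second.

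**Strata.** If the strata alone explained an assumed 5%, 10% or 20% of the variance of change, adjusting for them would give 57.2%, 59.5% or 64.6% power at 54 patients. In 20,000 simulated null trials with four balanced strata, the unadjusted t-test had a two-sided type I error of 4.9%, 3.7%, 2.8% and 2.0% when strata explained 0%, 10%, 20% and 30% of the variance. Omitting prognostic strata makes the test conservative.

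**The case against.** The strongest defence is that nothing here is an error. Under randomisation the change-score test is unbiased, its confidence interval already allows for chance baseline imbalance, and its type I error is not inflated. That stands, and it limits the point to efficiency.

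The size of the gain is also uncertain. The document gives neither rho nor the visit-specific SDs. The baseline scan falls within 15 days of STEMI and the second at six months, so equal variances cannot be taken for granted. No passage says that T2DM or infarct site predicts change in remote ECV. All of this stands: the gain may be close to nothing.

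The sensitivity mixed model may carry baseline and strata, which is ordinary content for an analysis plan not shown here. Even so, it would remain secondary to a primary test that cannot adjust.

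A reader might infer three stronger claims that the document does not support:
- *The analysis ignores baseline ECV.* It does not; it subtracts it.
- *Adjustment is equivalent to a definite number of extra patients.* Any such figure rests on an assumed ECV SD and on equal variances, and is not a bound.
- *Days from STEMI to baseline CMR must also enter the model.* Section 2.4 handles timing by design ("the baseline CMR was required to be performed within 15 days following STEMI, preferably before hospital discharge"), and no passage shows that timing within that window is prognostic.

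Adjustment also does not settle how missing six-month scans are handled; the same imputed values would enter either analysis.

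**Conclusion.** The point holds as a matter of efficiency and should be fixed. It does not threaten validity. The primary test adjusts for neither baseline ECV nor the stratification factors, although every randomised patient should have both.

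With equal variances at the two visits and assumed rho from 0.9 to 0.3, power with 54 complete patients would be about 57% to 74% against 55% unadjusted, less 2 to 3 points for estimating covariates. If ECV varies more at six months than at baseline, the gain can be near zero. Any gain from the strata depends on a prognostic value that the document does not give. Over the rho range shown, adjustment does not restore 80% power, so it can lessen the shortfall but not cure it.

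**What to change.** Before database lock and unblinding, make the primary analysis an ANCOVA of six-month remote ECV (or its change; the treatment estimate is the same once baseline is a covariate) on treatment, baseline ECV, T2DM and infarct site (anterior or non-anterior). Report the adjusted mean difference with its 95% confidence interval. Use the same approach for the other continuous CMR endpoints, and keep the unadjusted test as supportive. Leave days from STEMI to baseline CMR out of the primary model.

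The cost is a change of wording and a few degrees of freedom. Baseline ECV comes from the required baseline scan, and the two factors were needed to randomise, so no new data are required. The timing matters: an adjusted model chosen after unblinding would not carry the same weight.

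### An unspecified normality check picks between a t-test and a Mann–Whitney test for the primary endpoint, while the contrast, reported effect and sample size all concern means

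*Protocol article*

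**What the plan says.** All the relevant text is in section 3, Statistical Considerations, of the protocol article.

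- **Contrast:** "The primary analysis will compare the mean change in ECV of the remote myocardium from baseline to six months between treatment groups".
- **Test:** Student's t-test or Mann–Whitney U, "depending on whether the variable has a normal distribution". The article names no normality test or threshold. It does not say whether the check applies to the raw change, to residuals, to each arm or to the pooled data.
- **Reported effect:** "The mean differences will be reported along with 95% confidence intervals and two-sided" (the sentence ends with the p-values). This applies whichever test is used; no estimate is tied to the rank test.
- **Sample size:** the planning assumption is "Assuming a change of 1.5% ± 2.2 in the ECV for the placebo group and an 85% relative reduction in the experimental group". From it the article derives 47 evaluable patients per arm, 94 in all, for 80% power. The recalculation after early stopping gives 55% power with 54 patients under the same assumptions.
- **Missing data:** outcomes are filled by last observation carried forward; a missing baseline stays missing.
- **Other analyses:** a mixed model for repeated measures is a sensitivity analysis. Secondary and exploratory outcomes are to be analysed by similar methods. A detailed SAP is to be completed before lock and unblinding.

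**The concern.** Mann–Whitney asks whether values in one arm tend to be larger than in the other. That is the same question as a difference in means only under extra conditions, such as a pure shift with identical shapes. Under the rank branch, the p-value would therefore answer one question and the mean difference with its CI another. One could fall on the significant side while the other does not, and the article does not say which governs.

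Missing scans can drive the choice. Section 2.5.4 and Table 1 place CMR only at baseline and six months, so the last observation for a missing follow-up scan is the baseline scan and the change is exactly zero. A cluster of exact zeros is non-normal by construction. Missingness, rather than the behaviour of ECV, could then decide which hypothesis is primary.

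At about 55% power a borderline result is a realistic prospect, and that is where the choice of test matters most.

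**Working it through.** **1. The plan's own figures reproduce for a comparison of means.** Inputs from section 3: placebo change 1.5, SD 2.2, 85% relative reduction, alpha 0.05, two-sided; 1:1 allocation from section 2.5.1.

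- Difference: 0.85 × 1.5 = 1.275 points; standardised 1.275 / 2.2 = 0.58.
- n per arm = 2 × (1.96 + 0.842)² × 2.2² / 1.275² = 46.7, so 47, as stated. The noncentral t gives 47.7.
- Power at 27 per arm: 56.7% by normal approximation and 55.2% by noncentral t, against 55% stated.

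These figures are correct, and they are for a difference in means.

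**2. How often the rule switches and what follows.** I simulated 27 per arm with normal changes, means 1.5 and 0.225 (1.5 − 1.275) and SD 2.2, in 6,000 trials per scenario. Two inputs are assumptions. The check is Shapiro–Wilk at 5%, applied per arm, to pooled data or to within-arm residuals, because the article names none. The loss is a random 20% in each arm set to zero change; 20% is the article's planning figure, not an observed rate.

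| Planned effect | Complete data | 20% carried forward |
|---|---|---|
| Rule switches, per-arm check | about 10% | about 45% |
| Rule switches, pooled check | about 5% | about 43% |
| Rule switches, residual check | about 5% | about 25% |
| Tests disagree at 0.05, whichever is selected | about 7.5% | about 10% |
| Tests disagree and Mann–Whitney is selected | 0.4% (pooled) to about 1% (per arm) | about 5% (per arm or pooled); about 2.5% (residual) |
| Power: t / Mann–Whitney / rule | 55% / 52% / 55% | 45% / 41% / 43% (per arm) |

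With exactly 5 of 27 per arm set to zero (18.5%), the per-arm check switches in 33% of trials. The fifth row measures the conflict: it counts trials where the rank p-value is reported beside a t-based CI that points the other way.

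**3. Other shapes, complete data, planned shift** (8,000 trials each).

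- Heavy tails (t, 4 df): the rule switches in 43–52% of trials, and the two tests disagree in about 14%.
- Skewed (lognormal, sigma 0.6): the rule switches in 92–96%, and the tests disagree in 21–22%.

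**4. Type I error.**

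- Same distribution in both arms: 4.5–5.0% for the rule across normal, skewed and heavy-tailed data. With equal 20% carry-forward it is 4.9%.
- Equal means and SDs but different shapes (normal against skewed): 6.8–7.7% for the rule, against 5.5–5.6% for the t-test alone.

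**The case against.** The best defence is that the rule and both candidate tests are declared in advance. Section 2.5.1 keeps data analysts blind to allocation, and the normality criterion is a detail that an article may leave to the SAP. Under the planning assumption of a mean shift with one SD, both tests address the same null. The mixed model already supplies a mean-based check. The cost is small: about 2 points of power with 20% carried forward, and next to none with complete normal data.

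Much of this stands. A missing threshold alone would not be worth raising. What does not stand is that the SAP could settle the matter by adding one: the primary hypothesis would still depend on the data, and a mean difference would still be paired with a rank p-value. Blinding does not remove that mismatch, and a sensitivity analysis does not say which result is primary.

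A reader might infer three stronger things that the article does not support:

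- **The false-positive rate is inflated.** It stays near 5% when the arms share a distribution. The excess appears only in a constructed case of equal means with different shapes.
- **About 7.5% of trials would give a contradictory headline result.** That figure counts all disagreement between the tests, including trials where the rule keeps the t-test and the p-value and CI agree. The relevant figure with complete normal data is 0.4–1%.
- **The test would be chosen with sight of the treatment effect.** Nothing in the article says so, and its blinding text points the other way.

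**Conclusion.** The point holds as a defect in a rule that the article itself fixes: an unspecified check can move the primary p-value to a hypothesis that matches neither the stated contrast, nor the reported effect, nor the sample-size basis. The harm is an unfixed primary hypothesis and a possible mismatch between p-value and CI. It is small if changes are near normal and follow-up scans are complete, and grows to a conflict in up to about 5% of trials if a fifth of the changes are carried-forward zeros. These sizes rest on Shapiro–Wilk at 5%, on the planned effect and SD, and on equal random loss; only the effect, the SD and the 20% planning figure come from the article. The stated 47 per group and 55% power need no correction on this account. This should be corrected, but it does not threaten the validity of the trial.

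**What to change.** Delete the conditional choice in section 3 and carry the replacement into the SAP before lock and unblinding. Suggested text:

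*The primary analysis is a linear model of six-month remote ECV on treatment, baseline ECV, T2DM and MI location. The adjusted mean difference, its 95% CI and its two-sided p-value come from this model, whatever the result of any normality check. A Mann–Whitney test with a Hodges–Lehmann estimate and CI is a sensitivity analysis.*

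At minimum, the t-test alone would remove the defect; baseline adjustment is a preference beyond that. Its gain depends on the correlation between baseline and change, which the article does not give. With the SD multiplied by √(1 − r²), normal-approximation power at 27 per arm is about 57%, 61% or 69% for r = 0, 0.3 or 0.5.

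The same principle should apply to the secondary and exploratory outcomes that inherit the rule. Whether carrying the baseline forward is sound is a separate question that this change does not settle.

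The cost is one sentence, with no new data. The downside is lower power than a rank test if changes are far from normal. In the simulations the t-test had 58–59% against about 79% for Mann–Whitney under the skewed shape, and about 58% against 67% under heavy tails. The rank-based sensitivity analysis would show such a pattern but would not restore the lost power to the primary test.
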